### Study procedures

Both studies in the DROP share the same study time frame (May 2023 – December 2024), time points for data collection and study instruments. Each participant is followed for a 12-week study period with 5 research visits (on *t* = 0, *t* = 2, *t* = 4, *t* = 8 and *t* = 12 weeks) at which questionnaires will be administered (see Table 2 and Fig. 1). At the end of the 12-week study period, a selection of patients will be asked to participate in semi-structured interviews to evaluate the received care. The screening and allocation procedures are different in both studies and are described separately below.

**Table 2 Tab2:** Data collection schedule and measurement instruments

Data collection	Measurement instrument	Visit 1 *Week 0*	Visit 2 *Week 2*	Visit 3 *Week 4*	Visit 4 *Week 8*	Visit 5 *Week 12*
Baseline characteristics	Questionnaire on patient characteristics	X				
Dry mouth severity	Numeric Rating Scale (NRS) (11-point; from 0 to 10) [1, 31]	X	X	X	X	X
Dry mouth impact	Summated Xerostomia Inventory, shortened Dutch version (sXI-D, adapted) [32]	X	X	X	X	X
Oral health-related quality of life	Geriatric Oral Health Assessment Index, Dutch version (GOHAI-NL) [33]	X	X	X	X	X
Health-related quality of life	EuroQol 5 Dimensions 5 Levels (EQ-5D-5L) [34]	X		X	X	X
Functional status	Patient-reported functional status (PRFS) [35]	X	X	X	X	X
Patient-perceived effect	Global Perceived Effect, 7-point scale [36, 37]		X	X	X	X
Patient-reported medical costs	The Institute for Medial Technology Assessment (iMTA) Medical Consumption questionnaire (iMCQ, adapted) [38]	X		X	X	X
Medication changes	Changes in medication since the last visit		X	X	X	X
Adherence^a^	Short questionnaire on adherence		X	X	X	X
Side-effects^a^	Short questionnaire on side-effects		X	X	X	X

^a^This data is collected in the pilocarpine study only

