The second barrier is the absence of effective, pharmacological treatments with limited to no side-effects. Aside from symptom management through lifestyle, dietary and oral hygiene improvement and/or short-lasting saliva substitutes, there is just one (off-label) pharmacological option available in the Netherlands and most other countries: pilocarpine [17–19]. Pilocarpine is a parasympathomimetic and systemic drug that activates muscarinic receptors, thus increasing the secretion of natural saliva and alleviating symptoms of dry mouth. Systemic pilocarpine, however, has been associated with severe side effects, such as excessive transpiration, headaches, dizziness and frequent urination. The severity of these side effects often do not outweigh the benefits of the drug [20]. Therefore, current research focuses on topical administration of pilocarpine in the oral cavity (e.g. lozenges, drops or mouthwash). This has indeed been identified as a potentially effective treatment option for dry mouth with significantly fewer to no adverse side effects [20–22]. In fact, a previous pilot study of our research group has found that locally administered pilocarpine drops are effective in reducing xerostomia complaints with minimal side effects in older patients with xerostomia [21]. While this and other recent studies show promising results for topical administration of pilocarpine in patients with dry mouth, there is currently insufficient high level evidence due to the use of small sample sizes and the lack of double-blind placebo randomized controlled trials.

The DRy mOuth Project (DROP) attempts to contribute to better care for patients with dry mouth in the last phase of life by addressing the above-mentioned barriers with two separate intervention studies. The first barrier, the lack of knowledge and awareness, will be addressed by investigating a nurse-led patient education program in a cluster mixed-methods trial. The second barrier, the lack of an effective pharmacological treatment, will be addressed by investigating a topical form pilocarpine in a double-blind placebo randomized controlled trial.

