#### Pilocarpine study

The pharmacological study is a four-week double-blind placebo-controlled randomized trial with an eight week unblinded extension treatment period with off-label pilocarpine eye drops with 120 patients from either hospital or nursing home setting. The study intends to evaluate the effect of locally administered oral pilocarpine drops (3 × 5 mg of pilocarpine per day) in reducing complaints of dry mouth in a palliative population at the expense of limited adverse events, as compared to placebo. A double-blind placebo-controlled randomized controlled design was chosen to minimize response bias and achieve a high level of evidence.

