#### Pilocarpine study

Patients will be recruited in two hospitals (one university hospital, one regional hospital) and nursing homes affiliated with The Living Lab in Ageing & Long-Term Care. Recruitment and identification of eligible patients will be carried out by the hospital’s palliative care consultants and nursing homes’ nurses based on the inclusion and exclusion criteria. When an eligible patient has been identified, the care teams will hand over an information letter and the research team will be notified. After a minimum of 1 day, the research team will perform an informative visit to explain the study procedures and the application of the drops, answer any questions and further assess eligibility. After 7 days of deliberation time, formal written informed consent will be obtained. The inclusion procedure will then be followed by (block) randomization of the patient to either pilocarpine or placebo using ALEA®. The randomization outcome will be blinded for both the patient and the researchers. After randomization, the study will officially commence as visualized by Fig. 1.

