#### Baseline measures

Demographic characteristics of patients that will be collected are gender, age, care setting, primary diagnosis and co-morbidities, medication and treatment, presence of (partial) dental prosthesis and use of alcohol and nicotine. In addition, in the MEP study, the demographic characteristics of professionals that will be collected are function, years of experience, palliative care experience and education, and oral care experience and education.

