#### Secondary outcomes

Secondary outcomes include effect durability, (mouth-related) quality of life, patient-reported functional status, global perceived effect by participants, cost-effectiveness, adherence and side-effects. The specific research instruments per outcome used are detailed in Table 2.

Effect durability is measured by the percentage responders at week 8 and 12, as well as by changes in mean NRS dry mouth scores in the intervention versus the control group at all time-points. Effectiveness as perceived by the patient is measured by a 7-point scale (the Global Perceived Effect, GPE) [37] rating how much the patients’ condition has improved or deteriorated since the start of the study in both the control and intervention group. The global perceived effect is measured using a 7-point scale, rating how much the patients’ condition has improved or deteriorated since the start of the study for both the control and intervention group.

Changes in mouth-related quality of life is examined at all time-points between groups using two different validated questionnaires: the Geriatric Oral Health Assessment Index (GOHAI-NL) [33] and the shortened Summated Xerostomia Inventory (sXI-D) [32]. The GOHAI-NL consists of 12 oral health related items and three categories: physical function, psychosocial function and pain/discomfort. The sXI-D consists of 5 items, addressing dry mouth in general and consequences of dry mouth, such as difficulty eating and swallowing. In addition, functional status and overall quality of life are measured by a validated patient-reported functional status scale (from 0 = normal with no limitations to 4 = bed ridden, rarely out of bed) [37] and the EuroQol 5 Dimensions 5 Levels (EQ-5D-5L) questionnaire [34] respectively. The latter will also be used for the cost-effectiveness analysis and assesses quality of life in five dimensions: mobility, self-care, usual activities, pain/discomfort and anxiety/depression. The EQ-5D-5L is complemented by the iMTA (Institute for Medical Technology Assessment) Medical Consumption Questionnaire (iMCQ) for the cost-effectiveness analysis [38]. The iMCQ measures medical consumption, including medical and paramedical treatments or services, in- and outpatient care and medication.

Lastly, in the pilocarpine study the adherence and side-effects from either the pilocarpine or the placebo are measured by using short-form questionnaires.

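### The pilocarpine study schedules no side-effects assessment at week 0: the placebo comparison to week 4 stays unbiased but may be diluted, and patients started on pilocarpine have no untreated reference

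*Protocol article*

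**What the plan says.** All places are in the protocol article.

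- **Schedule.** In Table 2 (Study procedures) the row "Short questionnaire on side-effects" is marked at weeks 2, 4, 8 and 12, and the week 0 cell is empty. The footnote says "This data is collected in the pilocarpine study only".
- **Baseline data.** The Baseline measures section lists demographics and items such as "primary diagnosis and co-morbidities, medication and treatment, presence of (partial) dental prosthesis". It names no symptom checklist.
- **Aim.** Under Study design, Pilocarpine study, dry mouth is to be reduced "at the expense of limited adverse events, as compared to placebo". Side effects are also a secondary outcome.
- **Design to week 4.** "The pharmacological study is a four-week double-blind placebo-controlled randomized trial", and under Study procedures "The randomization outcome will be blinded for both the patient and the researchers". The Secondary outcomes section states that "side-effects from either the pilocarpine or the placebo are measured by using short-form questionnaires", so both arms are assessed.
- **Weeks 8 and 12.** Under Intervention and control, every participant is offered open-label pilocarpine for eight weeks after the blinded period.
- **Expected effects.** The Background attributes "excessive transpiration, headaches, dizziness and frequent urination" to systemic pilocarpine. The Ethical considerations section expects at most minor effects from topical use, namely irritation of the mouth and tongue.

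**The concern.** Several of the symptoms a pilocarpine questionnaire might cover are plausible complaints in frail or palliative patients before any drops are given. Headache, dizziness and frequent urination are examples. The expected local effect, oral irritation, also resembles the condition under treatment: the Background says dry mouth itself leads to burning and pain, and every participant enters with a severity score of at least 5.

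Without a week 0 value, a symptom reported at week 2 or 4 cannot be classed within a patient as new or old. If the questionnaire counts any current symptom, three things follow:

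- the crude rates in both arms overstate what the drops cause;
- the difference between arms shrinks, because patients who already have a symptom cannot newly acquire it;
- a chance difference between arms in pre-existing symptoms can be neither seen nor adjusted for.

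Tolerability is usually inferred from the lack of a difference, so dilution pushes towards the hoped-for conclusion. In the extension there is no concurrent placebo group, and the arm with the longest exposure to pilocarpine has no untreated observation to compare with.

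**Working it through.** No figure in the article rests on the week 0 cell. The only sample-size figure for this study concerns dry mouth severity. It reproduces: a 2-point difference, SD 3.8, two-sided alpha 0.05 and power 0.80 give 57 per group (114 in total). The article gives neither the power nor the sidedness for this study, so those two inputs are assumptions. The final size is 60 per group, used below.

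**Step 1: is the comparison to week 4 biased?** Let *b* be the share of patients with the symptom before treatment, equal in expectation across arms by randomisation, and let *d* be the share of the remainder who get it from the drug. With no new symptoms on placebo,

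expected difference = [*b* + (1 − *b*)*d*] − *b* = (1 − *b*)*d*.

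At *b* = 0.30 and *d* = 0.20 this is 0.70 × 0.20 = 0.140. A simulation of 100,000 trials with 60 per arm gave a mean difference of 0.140. The contrast is unbiased for the excess over placebo, but smaller than *d*.

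**Step 2: what does dilution cost?** Now allow new symptoms on placebo too. Let *d*₁ and *d*₀ be the incidence of new symptoms on pilocarpine and placebo among patients free of the symptom at baseline, and assume that existing symptoms persist. Then

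- any symptom: *p* = *b* + (1 − *b*)*d* in each arm, n = 60 per arm;
- new symptoms only: *d*₁ against *d*₀, n = 60(1 − *b*) per arm.

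For example, at *b* = 0.20, *d*₁ = 0.15 and *d*₀ = 0.03: any symptom is 0.20 + 0.80 × 0.15 = 0.320 against 0.20 + 0.80 × 0.03 = 0.224; new symptoms are 0.15 against 0.03 with n = 48.

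Power by exact enumeration, two-sided 5%:

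| *d*₁ v *d*₀ | *b* | Any symptom, rates (n = 60) | z test | Fisher | New symptoms, n per arm | z test | Fisher |
|---|---|---|---|---|---|---|---|
| 15% v 3% | 20% | 0.320 v 0.224 | 0.225 | 0.163 | 48 | 0.608 | 0.378 |
| | 30% | 0.405 v 0.321 | 0.159 | 0.115 | 42 | 0.548 | 0.320 |
| | 40% | 0.490 v 0.418 | 0.131 | 0.095 | 36 | 0.477 | 0.231 |
| 20% v 5% | 20% | 0.360 v 0.240 | 0.307 | 0.234 | 48 | 0.656 | 0.481 |
| | 30% | 0.440 v 0.335 | 0.220 | 0.166 | 42 | 0.595 | 0.443 |
| | 40% | 0.520 v 0.430 | 0.177 | 0.132 | 36 | 0.529 | 0.345 |

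All values of *b*, *d*₁ and *d*₀ are assumptions; the article gives none. Drop-out is ignored.

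**Step 3: chance imbalance.** The SD of the between-arm difference in a baseline symptom is √[2*b*(1 − *b*)/60]: 0.073, 0.084 and 0.089 at *b* = 20%, 30% and 40%. By the normal approximation, a gap of 10 points or more in either direction occurs in about 17%, 23% and 26% of trials.

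**Step 4: what reference does each arm have in the extension?**

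| Randomised to | Week 0 | Weeks 2 and 4 | Weeks 8 and 12 | Reference before pilocarpine |
|---|---|---|---|---|
| Placebo | not assessed | on placebo | offered pilocarpine | weeks 2 and 4 |
| Pilocarpine | not assessed | on pilocarpine | offered pilocarpine | none |

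**The case against.** The strongest reply is that the aim is comparative and the design answers it. To week 4 the study is randomised, blinded and placebo-controlled, and both arms complete the questionnaire, so the excess over placebo is the drug effect. That stands. A reader might infer from the empty week 0 cell that existing symptoms cannot be separated from drug effects; at group level to week 4 they can, as step 1 shows.

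Other points on that side:

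- **The instrument is not shown.** It is described as measuring effects of the drops and may ask about onset or change. If so, an empty week 0 cell is natural, as it is for adherence and Global Perceived Effect in the same table, and most of the dilution disappears. This stands as a condition on the point, although recalled onset is weaker evidence than a recorded baseline.
- **The symptoms named in the Background are those of systemic pilocarpine.** The trial drops are described as topical, with local irritation the expected effect. This stands: the assumed 20-40% background should not be read as tied to the effects expected of the drops. For oral complaints the week 0 GOHAI-NL, which has a pain/discomfort category, and the sXI-D give partial cover. Neither is a side-effects checklist.
- **The extension.** A reader might infer that nobody has a pre-treatment value there. That is wrong for the 60 patients planned for placebo, who have weeks 2 and 4. It holds only for those first given pilocarpine. The extension's stated purposes are longer-term efficacy and access to active treatment, so the placebo-controlled tolerability aim does not depend on it.
- **The power figures are illustrative.** The rates are assumed and the size depends on the test. Even the better analysis reaches only 66%, so failing to find a difference would owe much to having 60 per arm. This stands. The direction of the gain holds under both tests and in every row.
- **Burden.** The Limitations section says questionnaires were deliberately kept few. That is a real but small cost here.

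**Conclusion.** The point holds in a limited form. The article fixes a schedule with no side-effects value before treatment and names no baseline symptom checklist, in a study whose aim includes tolerability against placebo. This does not bias or invalidate the comparison to week 4. It costs precision and within-patient attribution, hides a baseline imbalance that could reach 10 points or more in roughly one trial in four to six under the assumed rates, and leaves the pilocarpine-first arm without an untreated reference in the extension.

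Under the assumed rates, analysing new rather than any symptoms raises power from 13-31% to 48-66% by the z test, or from 10-23% to 23-48% by Fisher's exact test. These ranges rest on background rates of 20-40%, new-symptom rates of 15% v 3% or 20% v 5%, full persistence of existing symptoms, no drop-out, and a questionnaire that does not already distinguish new from old symptoms. If it does distinguish them, little is lost. The point is minor: an inexpensive improvement, not a flaw that threatens the trial's conclusions.

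**What to change.** Add a mark at Visit 1 (week 0) in the side-effects row of Table 2, and ask the questionnaire's symptom items there before the first drops, worded as current symptoms and not as effects of the drops. State that new or worsened symptoms since week 0 will be compared by randomised arm to week 4. At weeks 8 and 12, report change from week 0 descriptively, separately for patients first on pilocarpine and first on placebo. If the questionnaire already records onset or worsening, say so in the article.

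The cost is one short form at a visit that already takes place: a few more minutes for a frail patient, with no change to sample size, visits or treatment. For patients already enrolled, week 0 cannot be recovered, so the baseline-adjusted analysis would apply only to those included after the change.

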#### MEP study

Within the MEP study, participating organizations are recruited through a regional network for nursing homes (University Network Care sector Zuid-Holland, UNC-ZH) and interprofessional connections with hospitals and nursing homes. Before the start of the study, all participating organizations are allocated to either the intervention arm (3 nursing homes, 3 hospitals) or control arm (3 nursing homes, 3 hospitals) on a first come, first serve basis (non-randomized).

Upon allocation to the intervention group, the participating nurses will first receive the MEP training before the inclusion of the first patient.

Eligible patients will be identified by the nurses and nurse specialists participating in the study with the help of the regular care teams on the wards of the hospitals and nursing homes. Identified patients will be provided with both oral and written information and an informed consent form on paper. After sufficient time for consideration (a minimum of 24 h), the patient will be asked to participate. Only after written informed consent, the study can commence.

Within the intervention group, all research questionnaires will be administered by the nurses as they are part of the anamnesis within the MEP consultation. Within the control group the questionnaires will be (telephonically) administered by a researcher.

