### Intervention and control

#### MEP study

The MEP is a patient education program and has been developed by our team to increase the use of guidelines by nurses in both hospitals and nursing homes, to strengthen awareness and knowledge in both nurses and patients and to improve management of dry mouth symptoms.

The structure and methods of the MEP were built on previous experience with patient education programs [26]. The content of the patient education program is based on existing palliative care guidelines [17–19] and has been reviewed by our multidisciplinary expert group, including palliative care researchers, an elderly care physician, a radiation oncologist, palliative care nurse specialists, an oral hygienist, a dentist and a patient representative. The program has also been piloted by two independent palliative care nurse specialists to ensure practical feasibility.

Table 1 shows the components and contents of the patient education program on dry mouth. The patient education program consists of a training for participating nurses, structured consultations with patients using the MEP handbook and patient information brochures. The MEP handbook is a guidebook, containing step-by-step plans for the initial and follow-up consultations, background information on dry mouth and oral care, conversation pointers and examples of different patient scenarios. To ensure the quality and uniformity of the patient education program, all participating nurses from the nursing homes and nurse specialists from the hospital based palliative care teams will be trained before the start of the study. This training consists of information on dry mouth characteristics, causes, consequences and treatment options. They will also learn to execute a structured MEP consultation, which includes anamnesis, oral inspection, patient education and treatment advice (Fig. 2). With each participant, these trained nurses will then execute a full MEP consultation on location at the baseline visit, and will monitor the symptoms in a shorter, structured consultation telephonically (or on location) at four different time points in week 2, week 4, week 8 and week 12 (see Fig. 1a).

**Table 1 Tab1:** Components and content of the Mouth Educational Program (MEP)

Components	Content of the components

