**Fig. 2 Fig2:**
[figure not shown]
Structure of the standardized MEP consultation. Using the MEP handbook, the trained MEP nurses and nurse specialists will perform a standardized consultation, including: evaluating the dry mouth complaint by anamnesis and oral examination, providing information on dry mouth care (patient education), creating a treatment plan by shared-decision making and reporting all findings and decisions in the patient’s medical records

The control condition is CAU, meaning dry mouth care as provided by the regular care team and uninfluenced by the research. No restrictions are placed on the care received and any research procedures, such as administration of questionnaires are handled by our research team.

Usual care practices, within and outside of research settings, are generally characterized by clinical heterogeneity due to differences on the individual professional level and the institutional level in awareness, knowledge, use of guidelines, training, resources, policies and so on [27, 28]. To allow for comparison between a structured form of dry mouth care (MEP) and existing practices (CAU) in two different care settings, for explanation of results, and for identification of barriers and facilitators to implementation, we have decided to collect usual care data through a self-developed questionnaire [27–30].

The institutions allocated to the control group will be offered the MEP training after they have completed the full study period (i.e. included all patients).

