#### Primary outcomes

The primary outcome is the effectiveness of the intervention in reducing dry mouth complaints in patients with a life-limiting condition or frailty. This is measured by the percentage responders at week 4, for which a clinically relevant response is defined as at least a 2-point reduction on the 11-point numeric rating scale (NRS). The NRS is a frequently used instrument in both clinical practice and research settings to score symptom severity, such as for pain, nausea and sleep [31]. The NRS for dry mouth ranges from 0 = no dry mouth symptoms to 10 = worst possible dry mouth symptoms [1, 7].

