#### MEP study

For this study, we expect the intervention group (patients who follow the MEP) to have at least 25% more responders (patients with clinically relevant less dry mouth at 4 weeks) than in the control group (patients who receive CAU). To test the null hypothesis (expected difference in responders at 4 weeks of 25%) with a power of 0.8, an alpha of 0.05 and an intra cluster coefficient of 0.10, we will need to include 181 patients which is obtained in 12 clusters (six hospitals and six nursing home clusters). Taking into account a 20% dropout rate at 4 weeks due to the frailty of our study population, 228 patients are needed. Each participating center is therefore expected to include 19 patients.

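### In the MEP study the nurse delivering the intervention asks for the primary outcome score in one arm and a research-team member asks in the other, so assessor and context are confounded with arm

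*Protocol article*

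**What the plan says.** Study procedures, MEP study, sets a different collection route for each arm. In the intervention arm, "all research questionnaires will be administered by the nurses as they are part of the anamnesis within the MEP consultation". The next sentence reads: "Within the control group the questionnaires will be (telephonically) administered by a researcher".

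Intervention and control, MEP study, shows that the nurses who ask are the ones who treat. After their MEP training, "these trained nurses will then execute a full MEP consultation on location at the baseline visit", and afterwards they "will monitor the symptoms in a shorter, structured consultation telephonically (or on location) at four different time points", namely weeks 2, 4, 8 and 12. For the control arm the same section states that "any research procedures, such as administration of questionnaires are handled by our research team".

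Primary outcomes defines the endpoint: "This is measured by the percentage responders at week 4, for which a clinically relevant response is defined as at least a 2-point reduction". The score in question is the patient's NRS, from 0 to 10. Sample size, MEP study, plans for "at least 25% more responders" in the intervention group.

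**The concern.** The NRS is a subjective score given by a patient who knows which care was received. No blinding, separate assessor or self-completion is described for the MEP arm. By week 4 the MEP patient reports to the nurse who has already given the baseline and week-2 consultations, and does so inside the next consultation. The control patient reports to someone with no part in the care.

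If patients grade their symptoms differently for the person who advised them, some will cross the 2-point threshold for that reason alone and be counted as responders. Having the same nurse ask at baseline does not cancel this, because at baseline she has not yet given any advice to credit. The Global Perceived Effect, which asks directly about improvement, is exposed in the same way.

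**Working it through.** **1. Comparison of the arms at the primary time points**

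- Assessor: MEP nurse in one arm, research-team member in the other. There is no overlap.
- Context: part of the intervention consultation in one arm, a research contact in the other. There is no overlap.
- Mode at baseline: on location for MEP, by telephone (in parentheses in the text) for control. This is a difference.
- Mode at week 4: telephone or on location for MEP, telephone for control. The two may coincide.

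Assessor and context are thus fixed by arm, while mode differs clearly only at baseline.

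**2. Can the analysis separate the two?** Data analysis specifies multi-level logistic regression for the MEP responder endpoint. No MEP patient is assessed by a researcher and no control by a treating nurse, so an assessor term would be identical to the treatment term. The cluster effect does not help, because arm is itself assigned by cluster.

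**3. Planned figures.** Sample size gives 181 evaluable patients, 12 clusters, an intra-cluster coefficient of 0.10 and 20% dropout.

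- 181 / 0.80 = 226.25, so 227; rounded up to equal clusters, 12 × 19 = 228. The stated total is reproduced.
- Patients per cluster: 181 / 12 = 15.08.
- Design effect: 1 + (15.08 − 1) × 0.10 = 2.408.
- Effective patients per arm: 181 / 2.408 / 2 = 37.6.

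The concern does not depend on these figures. They only scale step 5.

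**4. Illustration: reporting shift to responder rate.** All inputs here are assumptions: normally distributed change, SD of change 2 to 3, control responder rate p of 20 to 40%. If MEP scores are reported lower by s points on average, with no true effect, the MEP rate is Φ(Φ⁻¹(p) + s/SD).

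- s = 0.5, SD 3, p = 0.20: Φ(−0.842 + 0.167) = 0.250, a rise of 5.0 points.
- s = 0.5, SD 2, p = 0.40: Φ(−0.253 + 0.25) = 0.499, a rise of 9.9 points.
- s = 1, SD 3, p = 0.20: 0.306, a rise of 10.6 points.
- s = 1, SD 2, p = 0.40: 0.597, a rise of 19.7 points.

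The 0.5-point range is therefore about 5 to 10 points and the 1-point range about 11 to 20. A shift the other way acts in reverse: with s = −0.5, SD 2.5 and p = 0.30, Φ(−0.524 − 0.2) = 0.235, a fall of 6.5 points.

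**5. Illustration: chance of a false positive favouring MEP.** This takes no true effect, 37.6 effective patients per arm, control rates from 5 to 40% and a two-sided 5% test (2.5% nominal in this direction). For MEP rate p₁ and control rate p₀, power = Φ((p₁ − p₀ − 1.96·SE₀)/SE₁), where SE₀ uses the pooled rate and SE₁ the separate rates.

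- 5-point distortion: about 6 to 13%.
- 10-point distortion: about 14 to 30%.
- 15-point distortion: about 25 to 50%.

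**The case against.** A reader might infer four stronger claims that the article does not support.

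- **That the asymmetry is known to favour MEP.** No data on direction are given. The programme aims to raise awareness of dry mouth and includes an oral inspection, which could also raise reported severity. A shift favouring MEP is the more plausible direction, but it remains an inference.
- **That mode is also fully confounded.** MEP follow-up may be by telephone, so at week 4 the mode may be the same in both arms.
- **That a biased assessor is set against an independent one.** The article calls the control-arm assessor part of its own research team, and the same group developed the MEP. Nothing describes that person as independent or blinded.
- **That the pilot SD of 3.8 gives the size of the bias.** Sample size, Pilocarpine study, takes that figure from the pilocarpine pilot and does not describe it as an SD of change. It is not used above.

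Two points favour the plan. Table 1 lists anamnesis before education, so if that order is kept each score precedes that visit's teaching; at week 4, however, it still follows two earlier consultations. Keeping control nurses out of data collection also has a stated reason, that usual care should not be influenced by the research. That justifies the control-arm route but does not explain why the research team could not collect the NRS in the MEP arm.

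Finally, patients know which care they received, so some expectation effect remains whoever asks. This limits what the fix can achieve, but it is no reason to keep an avoidable difference.

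**Conclusion.** The concern holds for assessor and context. The plan measures its primary endpoint by a different person, in a different setting, in each arm, and the specified model cannot disentangle this from the effect of MEP. Limitations does not cover the issue: it discusses only the non-randomized allocation and regards that bias as confined to the organisational level, whereas differential reporting arises at each patient contact.

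The responder difference may be biased, plausibly towards MEP, by an unknown amount. The 5 to 10 points for a 0.5-point shift, and the false-positive chances, rest on assumed shifts, SDs and control rates. They show that a modest reporting difference would matter beside a 25-point target; they do not show that one exists. The change should be made because the difference is avoidable at low cost.

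**What to change.** Collect the NRS at baseline and week 4 in the same way in both arms, by one of two routes:

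- the research team that already contacts controls asks the item in both arms, with the same mode and script, before the nurse consultation in the MEP arm; or
- patients in both arms complete the item themselves, in the MEP arm before the consultation.

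State that only this value enters the primary analysis. Nurses may still ask the NRS for care. Preferably do the same at weeks 8 and 12 and for the Global Perceived Effect.

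The cost is one brief item or call for about 114 MEP patients per time point: 114 × 2 = 228 contacts for baseline and week 4, or at most 114 × 4 = 456 with weeks 8 and 12. It adds some scheduling around consultation dates and a small burden for frail patients. Sample size and intervention are unchanged.

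The first route equalises the assessor but does not provide a blinded one. Under either route, list the remaining expectation bias from unblinded self-report under Limitations. If collection can no longer be changed, list the assessor difference there too.
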